**Methods:**

The study will be conducted with adult male patients with SUD at a rehabilitation center and control volunteers. Participants will undergo a self-reported demographic and psychological assessment, a clinician-administered craving and emotional reaction test, and will also be monitored using a smartwatch. SUD participants will be monitored for a total of 18 months (6 months during rehabilitation, an additional 12 months post discharge), and control participants for a total of 6 months. All participants will be reassessed at the sixth month of monitoring. The collected data will then be used to train models with a neural network, which will then be validated against other models and compared with other algorithms. Demographic, psychological, digital biomarkers, and craving profiles will be created, correlations will be analyzed, and they will be compared with controls to generate a digital phenotype of SUD. When the model achieves adequate validity (area under the curve of ≥0.80), a graphic user interface will then be designed for clinical use.

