### Timeline

This study will include 2 types of observations: continuous passive monitoring and active surveys conducted at specific time points. Passive monitoring will occur continuously for 6 months in both groups, followed by an additional year for participants with SUD after their discharge from the treatment facility. Active surveys will be conducted at three time points: (1) baseline session or baseline, (2) 3 months after baseline, and (3) 6 months after baseline.

For digital monitoring purposes, smart bands provided to participants will be synchronized with a smartphone at the baseline session. Psychological assessment will be conducted within the first 15 days after baseline. Retesting will take place during the 15 days prior to the 6 months after baseline. Emotional reactions to cravings will be assessed at two points: (1) 3 months after baseline and (2) at 6 months after baseline (Figures 1A-1F).

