### Digital Measurement of Biomarkers

The Xiaomi Redmi Smart Band 8 will be worn on the user's nondominant hand, positioned 2 cm below the wrist bone and secured at a comfortable level, as instructed by the user manual. The device will be worn for a minimum of 22 hours per day, allowing for an anticipated loss of up to 2 hours of data due to activities such as recharging the device, synchronization with a smartphone, showering, and other routine tasks.

Physiological data, including heart rate (HR), peripheral capillary oxygen saturation, physical activity, stress, and sleep, will be collected using the device's shortest available measurement intervals. Data will capture periods of both high and low activity, during self-reported exercise, regular physical activity, and rest, and will identify any abnormalities in activity patterns.

Data synchronization, which facilitates upload to the associated Xiaomi account, will occur every 72 hours for all participants during the 6- or 18-month study period, as applicable. This data will be downloaded, preprocessed, and stored securely on an encrypted external hard drive and the institution's server for access by authorized research staff within 48 hours (Figures 2A-2E). Participants will receive a reminder notification if synchronization is not completed within 5 days.

Raw data will be used to compute digital the physiological features proposed in a MLM study by Rykov et al, [30] (Table 2).

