**Figure 5 figure5:**
[figure not shown]
Model’s possible outputs. These categories will be used as output labels of the predictive model and will allow the evaluation of the patterns detected from the input.

For the duration of the therapeutic process, the following labels will be used:

Timely rehabilitation: patients with SUD who complete the rehabilitation protocol within 7 months.Late rehabilitation: patients with SUD who complete the protocol in 7 months or longer.

Regarding relapse latency, the labels will include the following:

Early relapse: substance use occurring within the first 6 months post discharge.Late relapse: substance use occurring after 6 months but before the completion of 18 months post discharge.One-year maintenance: patients who have abstained from substance use at the end of the 18-month postrecovery period.

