## Results

The study is supported by the Program for the Improvement of Working Conditions for Members of the SNII and SNCA (PROSNII U006EST), and APPAC-VII-CUCS-2025 for Article Publication Fees, from the University of Guadalajara. The research protocol was approved by the University of Guadalajara (reference CI-01225) in January 2025. Recruitment of patients with SUD and control participants will take place from January 2025 through January 2027. As of June 2025, we have enrolled 35 participants, 18 patients with SUD and 17 controls. Data obtained from the device, as well as psychological and demographic data at baseline assessments and at 3 months are at the labeling and preprocessing stage of the data analysis. Results are expected to be published by the summer of 2028.

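### The relapse labels run to 18 months post discharge but follow-up stops at 12, so maintenance cannot be confirmed and half of the late-relapse window goes unobserved

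*Protocol article*

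**What the plan says.** **Follow-up.** The Abstract (Methods) states: "SUD participants will be monitored for a total of 18 months (6 months during rehabilitation, an additional 12 months post discharge". The Timeline section agrees, describing six months of passive monitoring in both groups, "followed by an additional year for participants with SUD after their discharge from the treatment facility". The section on digital measurement of biomarkers has data synchronized "during the 6- or 18-month study period, as applicable". In Table 1 the last scheduled time point is 18 months, for the SUD group only.

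**Labels.** The text under Figure 5 in the Output section gives three relapse classes:

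- "Early relapse: substance use occurring within the first 6 months post discharge".
- Late relapse: "substance use occurring after 6 months but before the completion of 18 months post discharge".
- "One-year maintenance: patients who have abstained from substance use at the end of the 18-month postrecovery period".

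**Calendar.** The Results section has recruitment running to January 2027 and adds: "Results are expected to be published by the summer of 2028".

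**The concern.** Two time horizons are given for the same endpoint. The follow-up sections use 18 months as a total from baseline. The late-relapse label counts 18 months from discharge. The maintenance class is named for one year but defined at 18 months. No section describes a visit, contact or monitoring between months 12 and 18 post discharge.

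These classes are not descriptive extras. The Output section makes them targets of the primary model, and the Validation and Verification section uses the output categories as the benchmark for judging the models, with AUC and F2 of at least 0.8 as the success criterion. A participant abstinent when monitoring ends at month 12 could, under the written definitions, belong to either late relapse or maintenance. Two people labelling the same patient from the same data could reach different answers. A clinical tool could also report 18-month abstinence on the strength of 12 months of observation.

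**Working it through.** **Inputs**

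- Follow-up: 6 months in rehabilitation plus 12 months post discharge (Abstract, Timeline).
- Late-relapse window: more than 6 and less than 18 months post discharge (Output).
- Maintenance: abstinent at the end of 18 months (Output).
- Last recruitment January 2027, publication by summer 2028 (Results).
- Relapse rate 60%, with no time horizon (Introduction).
- Minimum of 25 participants per group (Sample Size).

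**1. The stated total.** 6 + 12 = 18 months from baseline. This reproduces the figure in the Abstract and matches the last column of Table 1.

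**2. The horizon the labels need.** 6 + 18 = 24 months from baseline, which exceeds follow-up by 24 − 18 = 6 months.

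**3. Unobserved share of the late-relapse window.** The window lasts 18 − 6 = 12 months. Months 6 to 12 are observed and months 12 to 18 are not: 6/12 = 50%.

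**4. What each label can still do**

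| Label as written | Observable within 12 months post discharge? |
|---|---|
| Early relapse (0 to 6 months) | Yes |
| Late relapse, months 6 to 12 | Yes |
| Late relapse, months 12 to 18 | No |
| Maintenance at 18 months | Cannot be confirmed for anyone |

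**5. Illustration of mislabelling.** This applies only if staff keep the literal definition and call everyone abstinent at month 12 maintained. Assume a constant hazard with 60% relapsed by month T post discharge, so S(t) = 0.40^(t/T). The share of 12-month abstainers who relapse by month 18 is 1 − S(18)/S(12) = 1 − 0.40^(6/T). The number affected among 25, with everyone followed, is 25 × [S(12) − S(18)].

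| Assumed T (months) | S(12) | S(18) | Share mislabelled | Of 25 |
|---|---|---|---|---|
| 24 | 0.632 | 0.503 | 20% | 3.2 |
| 18 | 0.543 | 0.400 | 26% | 3.6 |
| 12 | 0.400 | 0.253 | 37% | 3.7 |

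The percentage depends heavily on T: at T = 6 it would be 60% (2.4 of 25). A hazard that falls over time gives smaller figures for a given 12-month abstinence.

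**6. Calendar.** January 2027 + 18 months = July 2028. January 2027 + 24 months = January 2029. The first date falls in the stated publication season; the second is after it.

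**7. Late discharge.** If 18 months were a fixed total, a patient discharged D months after baseline would have 18 − D months of post-discharge follow-up. For D = 7 that is 11 months, short of a year. The late-rehabilitation label (7 months or longer) shows that such patients are expected. The Figure 1 caption starts the SUD band after the first month of treatment. If the 7 months are counted from admission and baseline falls one month in, a 7-month discharge has D = 6 and exactly 12 months; only later discharges fall short.

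**The case against.** The strongest defence is that this is a slip in time origin, not a flaw in design. The Abstract, the Timeline, the synchronization text and Table 1 all fit 18 months from baseline. The class name fits 12 months post discharge, and so does the summer 2028 target. The word postrecovery in the maintenance definition is not defined in the article, so only the late-relapse label puts 18 months explicitly next to discharge. This explanation is probably right. It makes the correction easy, but it does not remove the need for one, because the two readings can label the same patient differently.

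Three stronger readings are tempting, and the article does not support them.

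- **That late relapse cannot be assigned at all.** Use in months 6 to 12 post discharge meets the written definition and is observed. Early relapse is unaffected.
- **That the model will be trained and scored on wrong labels.** This follows only if the 18-month definition is kept and applied to 12-month data. If staff label at 12 months, as the class name suggests, nobody is misclassified and only the written definition is wrong. The percentages above are conditional on that choice, on an assumed horizon and on a constant hazard. The counts also assume that all 25 are followed to the end, although the withdrawal and data-exclusion rules remove some participants.
- **That the calendar is impossible.** Under the stated follow-up, the last possible enrollee finishes about July 2028. That is tight, but it is not a contradiction. January 2027 is the outer limit of recruitment, and 18 SUD patients were already enrolled by June 2025. The dates clearly fail only under the literal label, so they are not separate evidence of error.

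**Conclusion.** The inconsistency is real, and the label definitions are wrong as written. Without any assumption beyond the article's own figures, the labels need 6 months more follow-up than is planned, 50% of the late-relapse window is unobserved, and maintenance cannot be confirmed for any participant. Two of the three relapse labels are affected, one of them only in its second half.

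How many participants would be mislabelled cannot be derived from the article. The range of about 20% to 37% of apparent maintainers is an illustration for the case where the literal definition is applied to 12-month data. Actual damage to the model is not shown, and the most probable intention (a 12-month horizon) would cause none once it is written down. The correction should still be made before any labels are assigned, because these classes define the model's target and its success criterion.

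**What to change.** Count all relapse labels from the actual discharge date and match them to the planned follow-up:

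- early relapse: use within 6 months;
- late relapse: use after 6 and up to 12 months;
- maintenance: no use through 12 months.

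State that the post-discharge year runs from actual discharge, as the Timeline section already says, and not to a fixed 18-month total from baseline. Patients discharged more than 6 months after baseline then also have a full 12 months. Bring the Abstract, the synchronization text and Table 1 into line with this time origin.

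**Cost.** No extra patients are needed. Monitoring becomes slightly longer for those discharged late, and the abstinence claim is 12 months instead of 18. For planning, a January 2027 enrollee who stays at least 6 months finishes about July 2028 at the earliest, which leaves little time before the stated publication date. Moving that date, or closing SUD enrolment sooner, would be a real cost beyond rewording, but the label correction does not depend on it.

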### Instruments

The study instruments that will be used in this protocol to measure each assessment category referred to in the timeline (Figure 1), are presented in Table 1.

**Table 1 table1:** Study instruments.

Instrument	Period				
	Baseline	3 Months	6 Months	18 Months	Continuous
Wearable: Xiaomi Redmi Smart Band 8^a^	✓	✓	✓	✓ ^b^	✓
Demographic survey^c^	✓				
The Adverse Childhood Experiences Assessment (ACEs)^d^	✓				
The University of Rhode Island Change Assessment Scale (URICA)^d^	✓				
The Alcohol, Smoking and Substance Involvement Screening Test (ASSIST)^d^	✓				
The Beck Depression Inventory (BDI-II)^d^	✓				
The Beck Anxiety Inventory (BAI-II)^d^	✓				
The Pittsburgh Sleep Quality Index (PSQI)^d^	✓		✓	✓^b^	
Wechsler Adult Intelligence Scale IV (WAIS-IV): Digit Span and Letter-Number Sequencing subscales^d^	✓		✓		
Emotional Pictures Database (EmoMadrid)^e^		✓	✓		
Mannheimer Craving Scale (MaCS)^e^	✓	✓	✓		
Automatic facial emotion recognition software (FER)^e^		✓	✓		

^a^Digital measurement of biomarkers.

^b^Substance use disorder group only.

^c^Demographic assessment.

^d^Psychological assessments.

^e^Emotional state during craving assessment.

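### The relapse labels run to 18 months after discharge but follow-up stops at 12, so one-year maintenance cannot be assigned as defined and late relapse is covered for only half its window

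*Protocol article*

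**What the plan says.** Methods, Output names three relapse classes as part of what the model must predict:

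- "Early relapse: substance use occurring within the first 6 months post discharge"
- "Late relapse: substance use occurring after 6 months but before the completion of 18 months post discharge"
- "One-year maintenance: patients who have abstained from substance use at the end of the 18-month postrecovery period"

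Follow-up is described in four places:

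- The Abstract (Methods) splits the 18 months of SUD monitoring as "6 months during rehabilitation, an additional 12 months post discharge".
- The Timeline gives six months of passive monitoring, "followed by an additional year for participants with SUD after their discharge from the treatment facility".
- Digital Measurement of Biomarkers says that data synchronization "will occur every 72 hours for all participants during the 6- or 18-month study period, as applicable".
- Table 1 (Instruments) ends with an 18-month column, after baseline, 3 and 6 months. Its entries carry the footnote "Substance use disorder group only".

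The four agree with one another: 18 months is the whole study period of a patient with SUD, and 12 of those months follow discharge.

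**The concern.** The same number, 18 months, is counted from two origins. In the follow-up plan it runs from baseline; in the labels it runs from discharge. The maintenance label also disagrees with its own name, which promises one year.

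These labels are the prediction target. Output presents them as the means of meeting the primary objective. Validation and Verification uses them as the benchmark for the AUC and F2 thresholds of 0.80, and the resulting model is meant for clinical use. A class defined by a status that nobody is scheduled to observe is either left empty or filled by a rule that the protocol does not state. If men abstinent at month 12 were reported under the 18-month definition, any relapse in months 12 to 18 would become a label error on the boundary between late relapse and maintenance.

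**Working it through.** **The plan's own total.** 6 months in rehabilitation + 12 months after discharge = 18 months from baseline. This reproduces the stated figure.

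**What the labels need.** 6 + 18 = 24 months from baseline. The gap is 18 − 12 = 6 months after discharge.

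| Label | Window after discharge | Observed under the stated schedule |
|---|---|---|
| Early relapse | 0–6 months | all |
| Late relapse | 6–18 months | months 6–12, i.e. 6/12 = 50% |
| One-year maintenance | status at month 18 | none |

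**Calendar check.** The Results section gives recruitment to January 2027 and publication by summer 2028. January 2027 + 18 months is July 2028; + 24 months is January 2029. Only the 12-month post-discharge reading fits.

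**Table 1 clock.** If a patient is discharged d months after baseline, an assessment at month 18 from baseline falls 18 − d months after discharge. That is 12 only when d = 6. For d = 8, as an example, it is 10. The late-rehabilitation label (7 months or longer) allows such discharges.

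**Illustration of mislabelling, if month-12 abstinence is reported as 18-month maintenance.** Assumptions: 25 patients with SUD (the stated minimum), no losses, and the 60% relapse rate from the Introduction, which has no time horizon there and is placed here at month 12 or at month 18. Let S(t) be the proportion still abstinent t months after discharge. With Weibull shape k (k = 1 is a constant hazard, k < 1 a falling one) and 60% relapse by month T:

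- S(t) = 0.4^((t/T)^k)
- share of men abstinent at month 12 who relapse by month 18 = 1 − S(18)/S(12)
- men mislabelled = 25 × [S(12) − S(18)]

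| Shape k | 60% reached by | S(12) | Share relapsing in months 12–18 | Men of 25 |
|---|---|---|---|---|
| 1 | month 12 | 0.400 | 36.8% | 3.7 |
| 1 | month 18 | 0.543 | 26.3% | 3.6 |
| 0.7 | month 12 | 0.400 | 26.0% | 2.6 |
| 0.7 | month 18 | 0.502 | 20.3% | 2.5 |
| 0.5 | month 12 | 0.400 | 18.6% | 1.9 |
| 0.5 | month 18 | 0.473 | 15.5% | 1.8 |

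First row in full: S(18) = 0.4^1.5 = 0.253; 1 − 0.253/0.400 = 0.368; 25 × (0.400 − 0.253) = 3.7.

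With a constant hazard and an 18-month relapse risk of 40% or 80% instead of 60%, the share is about 16% or 41%, or 2.8 or 3.5 men of 25.

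**The case against.** The strongest reply is that this is a slip of time origin and that the intended meaning can be recovered. The label is named one-year, four sections agree on 6 + 12 months, and the publication date fits. Investigators would then apply the label at study month 18, one year after discharge, and nobody would be mislabelled. As an account of the cause this is probably right, and it means the figures above are conditional, not expected losses. It does not remove the defect. The late-relapse definition names discharge as its origin, so whoever assigns labels cannot read it as counted from baseline.

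Three further objections stand in part.

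- A reader might infer that two of the three relapse classes cannot be scored at all. The documents do not support that: a relapse between months 6 and 12 after discharge lies inside the monitored period and meets the current definition. Only maintenance fails completely.
- A reader might infer that months 12 to 18 are certainly unobserved. The article shows only that no observation is described there. The full protocol could hold more, but it would then contradict the total and the split that the article states.
- The number of men is illustrative. The 60% is a general figure, the hazard shapes are assumed, 25 is a minimum, and losses under the withdrawal and data-exclusion rules are ignored.

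**Conclusion.** The point holds as a contradiction between stated rules for the primary prediction target, not as a missing detail. Under the schedule described, no patient has an observed status 18 months after discharge, so the maintenance label cannot be assigned as defined, and half of the late-relapse window has no described observation. This part is plain arithmetic and needs no assumptions.

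The size of any mislabelling depends on how the label is used. Applied at 12 months after discharge, it is zero. If the 18-month wording is kept for men seen abstinent at month 12, it is about 15% to 37% of those men, or roughly 2 to 4 of 25, under the assumptions listed with the calculation. It would go too far to say that 2 to 4 men will be mislabelled: the protocol gives neither a time horizon for its relapse rate nor a sign that the labels will be applied that way.

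The wording should be settled before any relapse outcome is labelled.

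**What to change.** In Output and Figure 5, end the labels where follow-up ends:

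- Late relapse: use after month 6 and up to month 12 after discharge.
- One-year maintenance: no use through month 12 after discharge.

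These replace both 18-month limits. They match the label's name, the stated follow-up and the calendar.

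State as well that the 18-month assessment in Table 1 is timed at 12 months after discharge. Changing the labels alone would not guarantee a full observed year for late-rehabilitation patients.

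The cost is the wording of two labels, Figure 5 and a Table 1 footnote, with no added visit. For a patient discharged later than 6 months after baseline, the final assessment moves to d + 12 months from baseline (20 months when d = 8). The Timeline's additional year after discharge already implies this, but for the last men enrolled it would fall after July 2028 (January 2027 + 20 months = September 2028), so the publication date should be checked.

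If 18 months after discharge is wanted, name it as a secondary label and add an outcome contact at that time. That needs 24 months from baseline, to about January 2029 for the last man enrolled, which is later than the planned publication.

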### Validation and Verification

All models and algorithms will undergo validation, verification, and testing using MATLAB’s tools for model evaluation and hyperparameter optimization. These processes will assess precision, performance, and recall metrics. Optimal model performance will be defined by achieving an area under the curve (AUC) of ≥0.80 and F2 score of ≥0.8.

The output categories will serve as benchmarks to evaluate the validity, reliability, and precision of the models. The validation dataset will be used to perform initial comparisons both within individual models of each algorithm and across different algorithms, replicating models with distinct architectures to refine performance.

For model verification, the test dataset will be used to determine final AUC and F2 scores. This final evaluation will confirm the models’ effectiveness as ML tools for predicting rehabilitation outcomes and informing clinical decision-making.

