### Blinding

Due to the nature of this study, neither the participants nor the first group of research staff will be blinded to group assignments. However, the group allocation of participant ID clusters will remain concealed from the second group of researchers. This second group will be responsible for data management, training the ML algorithm with the predictive model, and conducting validation, verification, and testing of the highest-performing models.

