### Data Preprocessing

Databases and labeling will initially be managed using Microsoft Excel (version 2412), after which MATLAB (version 2025a, MathWorks, Inc) will be used for data preprocessing. This process will include data cleaning and preparation to ensure the dataset is suitable for ML training.

Feature selection will be done following a filter methodology after correlation analysis to assess the correlation with the target and statistical measures. All data obtained through the wearable device, psychological assessment and ESDC will be scaled through a *z*-score standardization for dimensionality reduction and integration across all modality.

The data will be divided into training, validation, and test datasets using a k-fold cross-validation approach. The dataset will be split into k folds, with 2 folds randomly selected: one for validation and another for testing. The remaining k-2 folds will be used for training. The number of folds will vary depending on the specific model, enabling a broader experimental variance and improved model evaluation.

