### Algorithms

Modeling will be conducted using MATLAB, with ANN serving as the base algorithm. Additional algorithms, including decision trees, random forests, and support vector machines, will be used for validation. This multialgorithm approach will facilitate a comprehensive comparison of predictive accuracy across various models.

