The characteristics of the data and the results of ML training, validation, and verification may affect the algorithm’s performance. There is a possibility that the baseline algorithm designed for this project might not achieve the desired accuracy or generalizability, based on the participants recruited by the cutoff time of recruitment. In addition, the possibility of an algorithm better suited for smaller sample sizes could be considered at a later stage of this study based on the available data.

To address these risks, the study will follow established guidelines for developing and reporting ML predictive models in biomedical research [103]. These guidelines provide a comprehensive framework for reporting in research articles and outline structured steps for model development, aiming to reduce bias and ensure robustness in predictive modeling [77].

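### No single model is fixed before the test data are opened, so a best-of-several AUC and F2 result is not ruled out

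*Protocol article*

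**What the plan says.** All references are to the protocol article.

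- **Validation and Verification** opens with "All models and algorithms will undergo validation, verification, and testing". It then says "The validation dataset will be used to perform initial comparisons both within individual models of each algorithm and across different algorithms". The last step is "For model verification, the test dataset will be used to determine final AUC and F2 scores", followed by "This final evaluation will confirm the models’ effectiveness as ML tools".
- **Blinding** gives the second research group the task of "conducting validation, verification, and testing of the highest-performing models".
- **Data Preprocessing** splits the data into k folds, "with 2 folds randomly selected: one for validation and another for testing". The other k-2 folds are for training, and k may differ from model to model.
- **Algorithms** names the neural network as the base method and adds: "Additional algorithms, including decision trees, random forests, and support vector machines, will be used for validation".
- **Limitations and Considerations** allows that "the possibility of an algorithm better suited for smaller sample sizes could be considered at a later stage of this study", depending on the data available.
- **Pass mark.** Validation and Verification and Predictive Model both require AUC and F2 of at least 0.8. The Abstract starts work on the clinical interface on AUC of at least 0.80 alone.

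**The concern.** A held-out test set gives an unbiased estimate only if the choice of model is finished before the set is used. Here one section takes every candidate to the test stage and another takes several of the best. Neither names the model whose score answers the study question, or says how several test scores would be read together. If four candidates are scored and one clears 0.80, the text does not prevent that score from being reported as the result.

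The maximum of several noisy estimates is biased upward, and the noise is large when the test fold holds only a few men. The final AUC and F2 carry the study's stated hypothesis, decide whether the model is regarded as fully functional, and lead to a tool intended for clinical use. Optimism in these figures would pass straight into that decision.

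**Working it through.** **1. What the text fixes about the test stage**

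| Question | What the article gives |
|---|---|
| Which models are tested? | All (Validation and Verification); the highest-performing ones (Blinding) |
| What is the validation fold for? | Initial comparisons within and across algorithms |
| Does that comparison end with one locked model? | Not stated |
| Is the test set common to all models? | Not stated; k may vary by model |
| How are several test scores read? | Not stated |
| Must a later algorithm be adopted before testing? | Not stated |

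The first row is a contradiction. The others leave the consequence of that contradiction open.

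**2. Inputs for the size of the effect**

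The article gives no false-success probability, so there is none to reproduce.

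- From the article: at least 25 men per group (Sample Size); at least four algorithm families (Algorithms); thresholds of 0.80.
- Assumed: k = 5, so 50/5 = 10 men in a test fold (5 against 5) for patients versus controls, and 25/5 = 5 men (taken as 3 against 2) for a two-class outcome within patients; four candidate models, one per family; all scored on the same fold; no predictive information; between-model correlation from 0 to 0.8.

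**3. One uninformative model, tested once (exact)**

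AUC = U/(n1 × n2), where U is the Mann-Whitney statistic.

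- 5 against 5: AUC ≥ 0.80 needs U ≥ 20 of 25. The arrangements number 1+1+2+3+5+7 = 19 out of 252, so P = 19/252 = 0.075.
- 3 against 2: AUC ≥ 0.80 needs U ≥ 5 of 6. The arrangements number 1+1 = 2 out of 10, so P = 0.20.

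**4. At least one of four passes**

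For independent models, P = 1 − (1 − p)^4:

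- 5 against 5: 1 − 0.925^4 ≈ 0.27.
- 3 against 2: 1 − 0.80^4 = 0.59.

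Models trained on the same men are correlated, so the independent case is an upper bound under a common fold. The correlated cases, and those that add F2 ≥ 0.80, were simulated (20,000 runs, F2 at the midpoint cut-off).

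| Fold | Rule | One model | Best of 4, correlation 0.8 | 0.5 | 0 |
|---|---|---|---|---|---|
| 5 v 5 | AUC alone | 0.075 | 0.16 | 0.21 | 0.27 |
| 5 v 5 | AUC and F2 | about 0.035 | 0.09 | 0.11 | 0.13 |
| 3 v 2 | AUC alone | 0.20 | 0.37 | 0.46 | 0.59 |
| 3 v 2 | AUC and F2 | about 0.07 | 0.16 | 0.21 | 0.25 |

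The ratio of best-of-four to single model runs from 0.37/0.20 ≈ 1.9 to 0.13/0.035 ≈ 3.7, that is, roughly 2- to 4-fold.

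**5. Models with some skill**

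With a true AUC of 0.65, a 5 against 5 fold and correlation 0.5, a single model meets both criteria with probability about 0.13 and at least one of four with about 0.35. The mean of the best test AUC is about 0.79 against a true 0.65.

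**6. One model locked beforehand**

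The one-model column applies, and there is no inflation from this source.

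**The case against.** The strongest reply is that the article already has a three-way split. Comparison within and across algorithms is assigned to the validation fold, and the test fold is kept for final scores. No sentence says that models are chosen on test results. This stands as a partial safeguard. It is not complete, because the comparisons are called initial, nothing says they end in one choice, and the sections on testing speak of models in the plural.

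Several further points have weight:

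- **Any one pass as success.** A reader might infer that success means any model reaching the thresholds. The article does not say so: the Abstract and Predictive Model apply the criterion to a single model.
- **The same test data.** A reader might also infer a shared test set. Folds are drawn at random and k may vary by model, so this is not stated. Different folds would not cure the problem: the scores would be less alike and the models would be compared on different men.
- **A lead algorithm.** The neural network is the base method, and the plural in Blinding could mean one model per target. Both readings are fair, but neither fits an opening sentence that sends everything to testing.
- **The later algorithm.** Its stated reason is sample size and available data, not a failed test. Its timing is still left open.
- **AUC alone overstates the main rule.** This is right. Requiring F2 as well roughly halves the probabilities or better, so both sets are shown. The AUC-only figures remain relevant because the Abstract triggers the interface on AUC alone.
- **Detail left to a fuller document.** A journal article may omit the locking step. What it does state, however, is inconsistent between two sections, and that can be judged as it stands.

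**Conclusion.** The point holds in a limited form. The article disagrees with itself on which models reach the test data, and it does not fix one model per target beforehand. A best-of-several result is therefore not ruled out. It is not established that the reported figure will be the best of many tries.

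If several candidates were scored and the best reported, false success would rise about 2- to 4-fold. On AUC alone the rise is from 0.075 to 0.16-0.27 (5 against 5) and from 0.20 to 0.37-0.59 (3 against 2). Under the joint rule it is from about 0.035 to 0.09-0.13 and from about 0.07 to 0.16-0.25. These figures rest on the assumed five folds, 25 men per group, four uninformative models on a common fold and correlation of 0 to 0.8. The 3 against 2 case simplifies a relapse label that has three categories. Larger recruitment or fewer candidates would reduce the effect; more architectures would increase it.

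**What to change.** Reconcile Blinding with Validation and Verification, and state the following:

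1. For each prediction target, one model (algorithm, architecture, features and cut-off) is chosen on training and validation data and locked.
2. That model alone is scored, once, on a common untouched test set for the AUC and F2 criterion.
3. Other algorithms are compared on validation data. If they are also run on the test data, those results are labelled descriptive and do not count toward success.
4. Any alternative algorithm foreseen in Limitations and Considerations is adopted before the test data are opened.

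The cost is wording only. Recruitment runs to January 2027 and results are expected by summer 2028, so the rule can still be set in advance. The downside is that the reported AUC and F2 may be slightly less favourable.
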